#### Main hypotheses

Depressive symptoms (BDI-II scores) will be significantly lower in both study groups following the 3-month “Selfapy” programme compared to the control group.We expect higher depressive symptoms (BDI-II scores) in the unaccompanied group compared to the accompanied group.

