#### Secondary hypotheses

The drop-out rate is expected to be higher for the unaccompanied group than for the accompanied group.The strength of the therapeutic relationship will be significantly higher in the accompanied group than in the unaccompanied group.Positive attitudes towards Internet interventions will increase for the accompanied group as well as for the unaccompanied group when compared with reported attitudes at baseline. Increased scores in positive attitudes towards Internet interventions will be significantly higher for the accompanied group than for the unaccompanied group.Quality of life, social activation and self-esteem scores will increase significantly over the duration of the 3-month programme compared to scores taken at baseline and compared to scores in the control group. The increase in these parameters will be significantly higher for the accompanied group than for the unaccompanied group.

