**Target selection**		
First insights	In this module, the user is brought closer to the connection between thinking, feeling and acting. Based on this triangular connection, our course concept is explained to him/her.	Your personal triangles
Resources	Power sources are explained and gathered. Different methods are introduced to assist users in collecting power sources. Behavioural activation is prepared.	Evaluation daily protocol; power source images; treasure chest; resource walk
Behavioural activation	How to actively plan power sources during the day is explained.	Activity plan
Automatic thoughts	Automatic thoughts and thinking patterns are addressed.	Automatic thoughts; core beliefs
Realistic thoughts	The content of this module focuses on thinking about reality and thinking realistically.	Think realistically
Self-esteem	A positive self-concept is important for overcoming problems. The user learns how the concepts of self-confidence and self-acceptance can help to develop a positive self-image.	Positive self-image
Self-efficacy	The user is made aware of recent successes. This will enable him or her to better allocate his or her power reserves and increase confidence in his or her abilities.	“Your personal achievements—be proud of yourself”
Solve problem	Training to perceive a specific problem, gather potential responses in a problematic situation and develop the competence to implement a particular course of action to solve this problem optimally is introduced.	Problem-solving training
Mindfulness + excursus: pleasure training	In this module, mindfulness is the focus. A mindful approach is cultivated to improve stress management.	Mental note; mindfulness in everyday life; sitting meditation; body scan; your enjoyment moments
Social environment + stigma + social support	The focus of this module is on the environment and the social environment of the user. How social support can help to deal appropriately and successfully with stress is clarified.	“Difficult communication—your backing”
Relapse cases	Finally, a tool is introduced to help the user recognize when stress increases and becomes too much and how to handle it when the stress cannot be avoided.	Risk situations; early warning symptoms; first aid plan; relapse protocol

Subjects are advised to spend at least 15 to 20 min a day on the programme. If the modules are not processed for 3 weeks (recorded via login), this will be counted as the subjects drop out.

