Voluntary termination was handled according to the study programme. Researchers will go beyond the protocol to contact dropped-out participants and try to continue the collection of data.

In case of harm induced by the trial, even though this is unlikely as depicted above, there is insurance coverage for the study participants provided by Selfapy’s public liability insurance GmbH. There are no guidelines for stopping the study. The study design was approved by the ethics committee of the medical faculty of the Charité University Medicine Berlin.

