### Sample size

The between-group effect size estimate is based on meta-analytic evidence for the effect size observed in unaccompanied psychological interventions (*d* = 0.28) [16]. Treatment effect sizes in a sample with mild to moderately depressed subjects may be quite low. We conservatively reduced the estimated effect size to *d* = 0.23 [33].

Based on this effect size, a power of 0.80 and an alpha level of 0.05, we need a total of 200 subjects to address our hypotheses. The sample size was further estimated based on an expected drop-out rate of 50%. Drop-out rates in previous studies that used similar interventions ranged between 9% [9, 10] and 50% [34]. Based on this assumption, we would need a total of 400 subjects. The sample size was calculated using G-Power [35]. In addition, a comparison will be drawn between the unaccompanied and the accompanied versions of the online programme. The previously expanded experimental groups are compared to a control group, resulting in a total of three study groups to which the subjects are randomly assigned in a ratio of 2:2:1 (accompanied group: *n* = 160, unaccompanied group: *n* = 160, control group: *n* = 80).

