### Planned statistical analysis

The recorded data of the different measurement times (T1, T2, T3 and T4) for both intervention groups and the control group are analysed. The treatment results of all subjects (pre-post difference) are analysed using intention-to-treat (ITT) analyses.

The primary endpoint is the decrease in depressive symptoms in the BDI-II (Delta BDI-II) between study entrance (T1) and the end of the intervention (T3). A one-way ANOVA (within factor “group”) is performed to analyse the differences in the decrease of depressive symptoms between the intervention groups. A Bonferroni correction for multiple testing is applied to examine the expected group differences. This correction is carried out using the formula *α*/*n* (with alpha level *α* = 0.05 and *n* = number of tests) in order to lower the level of significance, make fewer results significant and thus the number of false-positive results reduce.

In an exploratory analysis, the basic effectiveness of the intervention compared to the control condition is examined (accompanied and unaccompanied group vs. control group) in order to counter the high drop-out rate.

In addition, the mean values including confidence intervals (95%) are recorded. The data are aggregated in the form of mean values and standard deviations. No interim analyses are planned.

To check the data obtained from the measuring instruments for normal distribution, the Kolmogorov-Smirnov test is calculated at the beginning. For this purpose, the mean values and standard deviations of each variable, as well as the Kolmogorov-Smirnov *Z*-value, are calculated, and the asymptotic significance (two-sided) is determined. Values below 0.05 indicate a violation of the normal distribution.

The intermediate measurements are analysed with regard to continuous outcome measures using repeated-measure ANOVAs. Independent *t* tests and *χ*^2^ tests are used to estimate the intergroup differences in sample characteristics prior to treatment.

Missing values in the data are replaced by multiple imputations, as well as “last-observation-carried-forward” (LOCF), “baseline-observation-carried-forward” (BOCF) and a “reference-based multiple imputation” method (“jump-to-reference” approach) to replace the missing values.

Effect size calculations to measure the therapeutic success (before and after the intervention) are carried out by dividing the difference between the respective group mean values by their pooled standard deviation.

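### Missing BDI-II values are to be filled by four methods with none named as primary; BOCF, and less strongly LOCF, can bias the accompanied versus unaccompanied contrast towards the main hypothesis

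*Protocol article*

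**What the plan says.** The relevant statements in the protocol article are these.

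- **Endpoint** (Planned statistical analysis): "The primary endpoint is the decrease in depressive symptoms in the BDI-II (Delta BDI-II) between study entrance (T1) and the end of the intervention (T3"). It is analysed by intention to treat.
- **Missing data** (same section): "Missing values in the data are replaced by multiple imputations, as well as “last-observation-carried-forward” (LOCF), “baseline-observation-carried-forward” (BOCF"), followed by reference-based multiple imputation, the "jump-to-reference” approach) to replace the missing values". No method is called primary and none is called a sensitivity analysis.
- **Main hypothesis on the two versions** (Main hypotheses): "We expect higher depressive symptoms (BDI-II scores) in the unaccompanied group compared to the accompanied group".
- **Predicted drop-out** (Secondary hypotheses): "The drop-out rate is expected to be higher for the unaccompanied group than for the accompanied group". Only the direction is given, and nothing is predicted for the control arm.
- **Planned loss** (Sample size): "The sample size was further estimated based on an expected drop-out rate of 50" per cent, which takes 200 subjects to 400.
- **Meaning of drop-out** (Intervention, below the course-content table): "If the modules are not processed for 3 weeks (recorded via login), this will be counted as the subjects drop out".
- **Data after drop-out** (Responses to crises and suicidality): "Researchers will go beyond the protocol to contact dropped-out participants and try to continue the collection of data".

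**The concern.** Two things are at stake.

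First, if the planned loss occurs, about half of the T3 scores in the intention-to-treat analysis are imputed. The imputation rule can then decide the trial. With four rules of equal rank, the choice of which result to report can follow the results.

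Second, two of the four rules are single imputations that stop a drop-out's improvement at a fixed point: at zero for BOCF, at the last observed value for LOCF. If one arm has more missing T3 scores, these rules turn that imbalance into a difference in symptoms. The arm predicted to lose more subjects is also the arm predicted to do worse, so the artefact points towards a main hypothesis. That contrast is the dismantling comparison for which the trial was designed.

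**Working it through.** **The plan's own figures.** 200 / (1 − 0.50) = 400, and 400 split 2:2:1 is 160 / 160 / 80. Both reproduce. The article therefore treats drop-out as lost sample at this step. How the 200 was obtained is a separate matter and is not used here.

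**Inputs.** From the article: 160 per active arm, alpha 0.05, a Bonferroni correction with the number of tests not given, planning effect d = 0.23, and drop-out higher in the unaccompanied arm. Assumed, because the article gives no values: a true mean change m = 8 points in both versions (so no true difference), SD of change 10, the proportion p with T3 missing in each arm, drop-outs who would have changed like completers, and 0.05/3 as the corrected level.

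**BOCF.** Missing subjects get a change of 0.

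- Arm mean = m(1 − p). Accompanied, 30% missing: 8 × 0.7 = 5.6. Unaccompanied, 50% missing: 8 × 0.5 = 4.0. False difference: 1.6 points.
- Arm variance = (1 − p)(100 + m²) − mean². Accompanied: 0.7 × 164 − 5.6² = 83.44. Unaccompanied: 0.5 × 164 − 4.0² = 66.00.
- Standard error = √((83.44 + 66.00)/160) = 0.966. Ratio: 1.6/0.966 = 1.66.
- Probability of rejection (normal approximation): about 38% at 0.05 and about 23% at 0.05/3.
- On the imputed data's own pooled SD, √((83.44 + 66.00)/2) = 8.64, the false effect is 1.6/8.64 = 0.185, against a planning effect of 0.23.

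**LOCF.** Assume every drop-out has a T2 score, half the gain (4 points) is reached by then, and the SD of that change is 8.

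- Arm means: 0.7 × 8 + 0.3 × 4 = 6.8 and 0.5 × 8 + 0.5 × 4 = 6.0. False difference: 0.8 points.
- A drop-out with no T2 score is carried forward from baseline, as in BOCF.

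**Range over the missing rates** (true change 8 points in both arms):

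| Missing, accompanied v unaccompanied | BOCF: false points | BOCF: rejects at 0.05 | BOCF: rejects at 0.05/3 | LOCF: false points | LOCF: rejects at 0.05 | LOCF: rejects at 0.05/3 |
|---|---|---|---|---|---|---|
| 50% v 50% | 0 | 5.0% | 1.7% | 0 | 5.0% | 1.7% |
| 45% v 55% | 0.8 | 14.3% | 6.6% | 0.4 | 6.7% | 2.5% |
| 40% v 60% | 1.6 | 42.5% | 26.6% | 0.8 | 12.1% | 5.3% |
| 30% v 50% | 1.6 | 38.1% | 23.0% | 0.8 | 11.8% | 5.2% |

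For 40% v 50% missing, BOCF rejects about 10% to 17% of the time at 0.05 for true changes of 6 to 10 points.

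**Active versus control under BOCF.** Take a true benefit of 0.23 SD and a control change of 0.3 SD (assumed), so the active change is 0.53 SD.

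- 50% missing in both: 0.5 × 0.53 − 0.5 × 0.3 = 0.115.
- Active 50%, control 20%: 0.5 × 0.53 − 0.8 × 0.3 = 0.025.
- Active 20%, control 50%: 0.8 × 0.53 − 0.5 × 0.3 = 0.274.

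The bias can go either way.

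**Jump-to-reference between the two active versions.** Take a true change of 8 in both versions and 5 in control (assumed), with 30% v 50% missing. The means are 0.7 × 8 + 0.3 × 5 = 7.1 and 0.5 × 8 + 0.5 × 5 = 6.5. A false 0.6 points remains, again in favour of the accompanied arm.

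**Multiple imputation under missing-at-random.** If drop-outs would have changed like completers, the expected difference is 0 and the test keeps its level. This follows from the assumption and was not simulated.

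**The case against.** **The ranking may be left to the analysis plan.** The article is condensed and the analysis plan is not shown. Multiple imputation is named first, so the other three can be read as sensitivity analyses. That reading is possible, but the sentence says that missing values are replaced by all four and labels none. The point is about what is written, not about an omission. Blinded data evaluation helps, but whether a contrast is significant under each method can be seen without knowing the arm labels.

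**The size rests on assumptions.** This stands. The article predicts only a direction. Rates of 30% and 50% in the active arms give 48 + 80 = 128 missing. The planned 50% overall (200 of 400) would then need 72 of 80 controls missing, or 90%. The 40% v 60% row fits 50% overall with 50% missing in control, and gives a similar answer. A smaller imbalance gives a much smaller one.

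**The difference may not be false.** This also stands. If drop-outs truly stay at their baseline or last value, carrying it forward is right. A reader might infer that LOCF and BOCF are certain to produce a false result. The documents support only that they can.

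**Control arm.** A reader might infer that BOCF must penalise the active arms because only they can drop out of the programme. That does not follow. BOCF acts on a missing BDI-II, control subjects can miss T3 too, and no control loss is predicted.

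**Non-use and missing outcome.** A reader might also infer that three weeks without module work leads to the T3 score being discarded. No passage says so, and the attempt to keep collecting data points the other way. What is left is that the article uses drop-out both for non-use and for lost sample, without saying which one triggers imputation.

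**Conclusion.** The point holds in this form. The article commits the primary endpoint to four imputation rules without a primary one, while planning for 50% drop-out. If missing T3 scores follow the predicted imbalance and drop-outs would have improved like completers, BOCF can push the accompanied versus unaccompanied contrast towards the main hypothesis, and LOCF can do so to a lesser degree. In the worked cases with a 20-point gap in missing rates, BOCF rejects about 38% to 43% of the time at 0.05 and LOCF about 12%. With a gap of 10 points or less the excess is modest, and with equal missingness it disappears. Bonferroni lowers the BOCF figure but does not restore the nominal level: in the 30% v 50% case it is about 23%, against 1.7%. No fixed direction of bias can be claimed against control.

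**What to change.** Before unblinding, amend the missing-data paragraph as follows.

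- Name one primary method: multiple imputation by arm under missing-at-random, using BDI-II at T1 and T2 and the other scales collected (QIDS-SR16 and BAI are taken at both visits), pooled by Rubin's rules.
- Label jump-to-reference as a sensitivity analysis for active versus control, and note that it is not conservative between the two active versions.
- Drop LOCF and BOCF, or keep them only as labelled supportive analyses that cannot decide the trial. Either resolves the ranking problem.
- State that imputation applies only when the T3 BDI-II was not obtained, so that an observed T3 score is used even if the subject was inactive in the programme.
- Report programme drop-out and missing T3 outcome by arm as separate quantities.

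The cost is wording only. No new data are needed, and there are up to two analyses fewer.

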## Discussion

The aim of this study is to evaluate the effectiveness of the online self-help programme “Selfapy” in a randomized-controlled-blinded parallel-group study. “Selfapy” was developed to become a low-threshold and affordable option for people dealing with depressive symptoms, especially for patients with subclinical to moderate depression symptoms (e.g. [16, 19]).

In this study, both accompanied and unaccompanied online intervention programmes are evaluated. This study will give further insight into the comparison of accompanied and unaccompanied variations within the same programme, which will add the value of the component of accompaniment (dismantling approach [37];).

In addition to our primary outcome (change of depressive symptoms), we will further investigate important other parameters such as life satisfaction, therapeutic relationships, social activation, self-esteem and attitudes. Additionally, an economic evaluation will be conducted from a healthcare perspective in future research.

Two weekly ACSA assessments in the intervention groups will allow us to identify meaningful patterns of early changes in life satisfaction during online treatment. These patterns will be investigated to predict the outcome at treatment termination and over the follow-up period, as well as drop-out rates or the number of times subjects participate in online treatment. These regular measurements may yield patterns that indicate the outcome of discontinuation of the treatment and allow for the follow-up period [38, 39].

A major strength of this study is the low-threshold criteria of inclusion, as anyone suffering from depressive symptoms can sign up through the study website without further requirements. These measures will improve the external validity of our study. This strength may also be regarded as a limitation, as it may result in a relatively heterogeneous group of patients [33]. The limitations of the study include the possibility of the parallel use of the health system, which could cause changes in symptoms, although we assess the healthcare use by questionnaires. It should also be taken into consideration that primary diagnoses other than depression are also included in the study.

The main article and several minor articles are pinned to the present study. The publication takes place in appropriate topic-specific journals. Any changes that differ from the present protocol will be openly communicated when the main article and any secondary articles are published.

## Conclusion

We evaluate the efficacy of the self-help programme “Selfapy” that offers low-threshold treatment to various patients also with mild to moderate depressive symptoms. By the dismantling approach, we can investigate the value of accompanied vs. unaccompanied variations within the same programme. Positive and meaningful results are expected in this study, which may have an impact on the acceptance and implementation of such programmes.

## Trial status

Regulatory approval was issued by the ethics committee of the Medical Faculty of the Charité University Medicine Berlin on 24 May 2019 (protocol version number is 2:00 dated 27 January 2021). Recruitment started on 24 June 2019; the number of recruited participants on 28 May 2020 was *n* = 298, and recruitment is ongoing.

## Trial registration

The trial has been registered on the German Clinical Trials Register (DKRS) (14 June 2019), with identifier number DRKS00017191.

The study protocol has been reported in accordance with the Standard Protocol Items: Recommendations for Clinical Interventional Trials (SPIRIT) guidelines.

## Data Availability

There are no plans to give public access to the participant level code. Only the study director, the study coordinator, the doctoral candidate and the student employees of the research group have access to the test data set.

## Abbreviations

ACSA: Anamnestic Comparative Self-Assessment
APOI: Attitudes towards Psychological Online Interventions Questionnaire
Bado: Basic documentation
BAI: Beck Anxiety Inventory
BDI-II: Beck Depression Inventory-II
CBT: Cognitive behaviour therapy
HRSD-24: Hamilton Depression Scale
CI: Confidence interval
iCBT: Internet-delivered cognitive behaviour therapy
MINI: Mini International Neuropsychiatric Interview
RCT: Randomized controlled trial
SASS: Social Activity Self-Assessment Scale
SMD: Standardized mean difference
SWOP-K9: Self-Efficacy, Optimism and Pessimism Scale
QIDS-SR: Quick Inventory of Depressive Symptomatology Self-Report
WAI: Working Alliance Inventory
WHOQOL-BREF: WHO Quality of Life-BREF
